### Data collection, management and analysis

#### Data collection and management

Study data will be primarily collected and managed using the REDCap tool hosted at the University of Sydney. REDCap is a secure, web-based application designed to support data capture for research studies [36]. Where hard copy questionnaires have been completed, they will be transcribed into REDCap by the research staff and the original scanned and uploaded to REDCap. We will collect MBS and PBS data from the Australian Commonwealth Department of Human Services (DHS) at the completion of the trial. Hard copy consent forms will be scanned and stored on a University of Sydney or University of Melbourne server, and the original form locked in a filing cabinet until it is sent to the DHS at the end of the trial. Study data, including MBS and PBS consent forms, will be retained for 15 years after which time it will be destroyed.

### Statistical methods

#### Sample size estimation, power and justification

Primary endpoints are at the patient level and are defined as changes in knee pain and function at 12 months. We wish to detect an effect size of 0.30 (moderate) [67]. Our sample size accounts for clustering effects due to people treated within the same GP practice. Assuming a minimum of 2 GPs per practice, 13 patients per GP practice recruited, with a coefficient of variation in practice size of 0.5, an intra-cluster correlation of 0.05 and up to 20% attrition of both GPs and patients, a total of 44 general practices and 572 patients will be required to detect the effect size with 80% power (two-sided significance level of 5%).

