**Methods:**

We will conduct a mixed-methods study, including a two-arm, cluster randomised controlled trial, with quantitative, qualitative and economic evaluations. We will recruit 44 general practices and 572 patients with knee OA in urban and regional practices in Victoria and New South Wales. The interventions will target both general practitioners (GPs) and their patients at the practice level. Practices will be randomised at a 1:1 ratio. Patients will be recruited if they are aged ≥45 years and have experienced knee pain ≥4/10 on a numerical rating scale for more than three months. Outcomes are self-reported, patient-level validated measures with the primary outcomes being change in pain and function at 12 months. Secondary outcomes will be assessed at 6 and 12 months. The implementation intervention will support and provide education to intervention group GPs to deliver effective management for patients with knee OA using tailored online training and electronic medical record support. Participants with knee OA will have an initial GP visit to confirm their diagnosis and receive management according to GP intervention or control group allocation. As part of the intervention group GP management, participants with knee OA will be referred to a centralised multidisciplinary service: the PARTNER Care Support Team (CST). The CST will be trained in behaviour change support and evidence-based knee OA management. They will work with patients to develop a collaborative action plan focussed on key self-management behaviours, and communicate with the patients’ GPs. Patients receiving care by intervention group GPs will receive tailored OA educational materials, a leg muscle strengthening program, and access to a weight-loss program as appropriate and agreed. GPs in the control group will receive no additional training and their patients will receive usual care.

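### The stated 80% power does not follow from the printed sample size inputs, which give about 72% with the stated patient attrition unless an unstated baseline correlation was used

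*Protocol article*

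**What the plan says.** In the protocol article, Statistical methods, under Sample size estimation, power and justification, one sentence gives both the inputs and the result. The target is a standardised effect of 0.30 on change in knee pain and function at 12 months. The inputs are "13 patients per GP practice recruited", "with a coefficient of variation in practice size of 0.5", and "an intra-cluster correlation of 0.05 and up to 20% attrition of both GPs and patients", with a two-sided 5% level. The result is that "a total of 44 general practices and 572 patients will be required to detect the effect size with 80% power".

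The Abstract confirms that these are recruitment numbers: "We will recruit 44 general practices and 572 patients with knee OA". The sample size paragraph mentions no baseline-to-follow-up correlation and does not say which SD standardises the 0.30. The Statistical analysis section does plan to adjust for the baseline value of the outcome. It also excludes practices that recruit nobody or withdraw before any patient data are collected.

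**The concern.** Since 44 × 13 = 572, the total is the number before attrition. A recruited total that allows for clustering, unequal practice sizes and 20% loss should be clearly larger than the number needed at analysis. Here the two almost coincide, so the 80% looked unsupported by the list of inputs beside it.

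Power of 80% for 0.30 is the trial's declared sensitivity for its primary outcomes. If it is overstated, a null result could be read as stronger evidence against an effect of 0.30 than the design supports.

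**Working it through.** **Inputs.** Effect d = 0.30; two-sided 5% (z = 1.96); 80% power (z = 0.8416); m = 13 recruited per practice; CV = 0.5; ICC = 0.05; attrition up to 20%. All come from the sample size paragraph. Allocation is 1:1 (Abstract; Randomisation and allocation concealment).

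**1. Individually randomised total.** 4 × (1.96 + 0.8416)² / 0.30² = 4 × 7.849 / 0.09 = 348.8, about 349.

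**2. Design effect for unequal clusters.** DE = 1 + [(1 + CV²) × m − 1] × ICC.
- m = 13: 1 + (16.25 − 1) × 0.05 = 1.7625
- m = 10.4 (13 × 0.8): 1 + (13 − 1) × 0.05 = 1.60
- m = 8.32 (10.4 × 0.8): 1 + (10.4 − 1) × 0.05 = 1.47

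**3. Reproducing 44 and 572.** Two quite different routes reach the plan's total.
- *Total not inflated for attrition:* 349 × 1.60 = 558; 558 / 13 = 42.9 practices; the next even number is 44, and 44 × 13 = 572. The value 1.60 comes from m = 10.4 with CV 0.5, or from m = 13 with CV 0.
- *Both attritions included, with an assumed baseline correlation r = 0.6:* 349 × (1 − 0.36) = 223; × 1.60 = 357 analysed; / (0.8 × 0.8) = 558; / 13 = 42.9, again 44 practices and 572 patients. The r = 0.6 is an assumption made here and is not in the article.

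**4. Power from the printed inputs alone.** Effective N = analysed N / DE. Power = Φ(0.30 × √(effective N / 4) − 1.96). Effect detectable with 80% power = 2 × 2.8016 / √(effective N).

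| Scenario | Analysed | DE | Effective N | Power for 0.30 | Effect at 80% power |
|---|---|---|---|---|---|
| No attrition (44 × 13) | 572 | 1.7625 | 324.5 | 77% | 0.31 |
| 20% patient loss (44 × 10.4) | 458 | 1.60 | 286 | 72% | 0.33 |
| 20% of practices also lost (35.2 × 10.4) | 366 | 1.60 | 228.8 | 62% | 0.37 |
| GP loss reduces patients within all 44 practices (44 × 8.32) | 366 | 1.47 | 249 | 66% | 0.36 |

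**5. Sensitivity to method.**
- A t reference with practices minus 2 degrees of freedom gives 75%, 70%, 60% and 64% for the four rows.
- A relative-efficiency correction for unequal clusters gives about 73% for patient loss and 63% with practices also lost.
- Ignoring the CV altogether gives 75% and 66% for those two cases.
- Dropping both the CV and all attrition gives effective N = 572 / 1.60 = 357.5 and 81%, but that discards two stated inputs.

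**6. What baseline adjustment would have to supply.** With 0.30 in units of the unadjusted SD, adjustment divides the variance by 1 / (1 − r²), so 80% needs effective N / (1 − r²) = 348.8.
- Patient loss: r = √(1 − 286 / 348.8) = 0.42
- Practices also lost: r = √(1 − 228.8 / 348.8) = 0.59
- At r = 0.5: 286 / 0.75 = 381 gives 83%; 228.8 / 0.75 = 305 gives 74.5%

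**The case against.** The strongest reply is that the planned analysis adjusts for baseline, which the figures in the table ignore. The article condenses a fuller protocol, and a correlation is the kind of input that may stand only there. With r = 0.6 the plan's total is reached with both attritions fully counted, at 81% power. This stands in part. It defeats two readings that a reader might infer. One is that the shortfall exists because attrition was left out of the total. The match to 558 is suggestive, but the second route gives the same total, so the article does not show the cause. The other is that the trial simply has 72% or 62% power. Those figures describe an unadjusted comparison and may be too low for the planned test.

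The reply does not rescue the paragraph itself. The paragraph prints a list of inputs and a result that disagree. This is not a complaint that a detail was omitted. The gain from adjustment also depends on which SD defines the 0.30: if it is already the SD after baseline adjustment, there is no gain at all.

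Three further points are fair:
- The text says attrition of GPs, not of practices. Each practice has at least two GPs and outcomes are patient surveys, so a departing GP need not take any data along. The 62% is therefore one conditional reading.
- The 20% is a ceiling. At 10% patient loss, 44 × 11.7 = 515 analysed, DE = 1.68, effective N = 306 and power is 75%.
- Multiple imputation is planned, but it does not generally restore lost information, and even complete data on all 572 give only 77%.

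**Conclusion.** The concern holds as a mismatch between the printed inputs and the printed result. With no variance reduction from baseline adjustment, the stated 80% is missed under every reading of those inputs: 77% with no attrition, 72% at the maximum patient attrition, and 62% or 66% when GP loss is added, depending on what that loss means. The figures rest on the usual design effect for unequal clusters and a normal approximation. The alternatives tried with all stated inputs kept do not bring the attrition cases near 80%.

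The article does not establish why the figure is 80%, nor that the planned baseline-adjusted test falls short of it. An adequate correlation could justify the figure, but the article would then need to say so.

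**What to change.** Keep 44 practices and 572 patients and correct the sample size paragraph in one of two ways.

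- *If 80% did not rely on baseline adjustment:* restate it as about 72% power for 0.30 with 20% patient loss, adding 62% if practices are also lost or 66% if only their patients are. Equivalently, state 80% power for 0.33 (0.37 with practices also lost).
- *If 80% relied on the planned baseline adjustment:* state the assumed correlation and which SD standardises the 0.30. With the unadjusted SD, at least about 0.42 is needed for patient loss, or 0.59 if practices are lost too. Power over a range such as r = 0.4 to 0.6 would show how far the claim depends on it.

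In either case, say whether GP attrition means loss of whole practices.

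The cost is wording only. The stated figure may become less favourable, but no extra patients and no change of design or analysis are needed.

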#### Statistical analysis

GP practices and individual participants will be analysed according to their randomised group, using intention-to-treat. Those practices that fail to recruit any patients or withdraw from the study prior to collecting data from any patients will be excluded from the analysis [68]. Descriptive statistics at the participant and GP practice level will be presented to allow comparison of treatment groups at baseline. Analyses will be conducted at the participant level. For continuous outcome measures, differences in mean change (baseline minus follow-up) will be compared between groups using generalised estimating equations (GEEs) to account for within-practice correlation with exchangeable correlation, robust standard errors, and adjusting for the baseline value of the outcome variable and stratification variables. For binary outcomes, GEEs will be fitted using a logit link function assuming an exchangeable correlation structure and robust variance estimation, adjusting for stratification variables, with results presented as odds ratios. To aid interpretation, risk differences will also be calculated using marginal probabilities [69]. Multiple imputation will be applied to missing participant-level data from GP practices which do not withdraw from the study before data collection and that recruit at least one patient [70].

An independent Data Safety and Monitoring Board (DSMB) will meet periodically to monitor the quality of trial data and the safety of patients. The DSMB may recommend continuing the trial or modifying the trial, or stopping the trial early. A recommendation to stop the trial may only be made to protect the safety of trial participants if there is clear evidence of a clinically important harmful effect.

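### Exchangeable GEEs with robust standard errors on at most 44 unequal practices: as usually implemented, two-sided type I error is about 7–8%, not 5%

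*Protocol article*

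**What the plan says.** Under Statistical analysis, the article compares mean change in continuous outcomes using "GEEs) to account for within-practice correlation with exchangeable correlation, robust standard errors", adjusted for the baseline value and the stratification variables. For binary outcomes, "GEEs will be fitted using a logit link function assuming an exchangeable correlation structure and robust variance estimation". Neither sentence names a small-sample correction, a reference distribution or degrees of freedom.

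Under Sample size estimation, power and justification, "a total of 44 general practices and 572 patients will be required", on the basis of "13 patients per GP practice recruited, with a coefficient of variation in practice size of 0.5" and "an intra-cluster correlation of 0.05 and up to 20% attrition of both GPs and patients". The test level is set there: the sample "will be required to detect the effect size with 80% power (two-sided significance level of 5"%).

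Under Randomisation and allocation concealment, practices are allocated 1:1, stratified by practice size (two levels) and location (two levels). Statistical analysis also removes practices that contribute no patient data, so the analysed number can be below 44 but not above it.

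**The concern.** The sandwich variance is justified as the number of clusters becomes large. With few clusters the fitted residuals are smaller than the true errors, so the variance is biased downwards. The estimated standard error is also itself noisy, which a normal reference ignores. Unequal cluster sizes and cluster-level covariates make both problems worse.

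All of these conditions are present here: about 22 practices per arm, a coefficient of variation of 0.5 in practice size, and three between-practice effects (arm, size, location) besides the intercept. At stake is the stated two-sided 5% level for both primary outcomes, pain and function at 12 months. The coverage of the confidence interval for every secondary outcome analysed by GEE is affected in the same way.

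**Working it through.** **Inputs from the article.** 44 practices × 13 patients = 572, which matches the planned total; 44 / 2 = 22 practices per arm. Coefficient of variation (CV) 0.5, intra-cluster correlation (ICC) 0.05, two-sided 5%. With 20% patient attrition, 13 × 0.8 = 10.4 completers per practice. As a sensitivity case, 44 × 0.8 = 35.2, so about 35 practices.

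**Assumptions not in the article.** Baseline–outcome correlation 0.5; about half the practices large; about 35% regional; gamma-distributed practice sizes.

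**Method.** Data were simulated with no treatment effect. An exchangeable GEE was fitted with arm, baseline, practice size and location. The plain sandwich standard error (SE) was used and the null rejected when |estimate / SE| > 1.96. There were 10,000 trials per row. At a true 5%, the Monte Carlo standard error is √(0.05 × 0.95 / 10,000) = 0.22 points.

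| Practices | Mean size | CV | ICC | Mean SE / true SD | Type I, plain sandwich, normal | Type I, Mancl–DeRouen, normal |
|---|---|---|---|---|---|---|
| 44 | 13 | 0.5 | 0.05 | 0.925 | 7.7% | 5.0% |
| 44 | 10.4 | 0.5 | 0.05 | 0.937 | 7.2% | 4.6% |
| 44 | 10.4 | 0.5 | 0.01 | 0.932 | 7.6% | 4.7% |
| 44 | 10.4 | 0.5 | 0.10 | 0.924 | 7.6% | 5.0% |
| 44 | 10.4 | equal | 0.05 | 0.953 | 6.7% | 4.6% |
| 35 | 13 | 0.5 | 0.05 | 0.922 | 8.1% | 4.6% |
| 35 | 10.4 | 0.5 | 0.05 | 0.915 | 8.3% | 4.6% |
| 30 | 10.4 | 0.5 | 0.05 | 0.895 | 9.1% | 4.8% |

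**Size of the SE shortfall.** With CV 0.5 and ICC 0.05 at 44 practices it is 1 − 0.937 = 6.3% to 1 − 0.925 = 7.5%; with equal sizes, 1 − 0.953 = 4.7%. At 35 practices it is 7.8% to 8.5%.

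**Hand check.** If the SE were a fixed fraction r of the truth, the error would be 2 × [1 − Φ(1.96 r)]. For r = 0.937 this is 2 × [1 − Φ(1.837)] ≈ 6.6%; for r = 0.925 it is 2 × [1 − Φ(1.813)] ≈ 7.0%. Bias alone therefore explains most of the excess. The rest, up to the simulated 7.2% and 7.7%, comes from variability of the SE.

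**Other runs.**
- A standard GEE library (1,000–1,500 trials per row) gave SE ratio 0.954 and error 7.7% at 44 practices, 0.934 and 7.3% at 35, and 0.911 and 7.8% for a logit model at 44. The binary analyses are therefore affected too.
- Runs using the planned stratified blocks of 8, 10 and 12 gave 325/4,200 = 7.7% at 44 practices and 351/4,200 = 8.4% at 36, with ratios of about 0.91 and 0.90.
- A further set of 3,000 trials per scenario gave about 8% at 44, 8.2% at 36 and 6.2% with equal sizes.

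**What does and does not repair it (CV 0.5, ICC 0.05).**
- Scaling the plain variance by K/(K−1), where K is the number of practices: still 7.0–7.4% at 44.
- Plain sandwich with t(K−2): still 6.5–7.1% at 44 and 7.2–7.3% at 35.
- Variance scaled by K/(K−5) with t(K−5): 5.2–5.6% at 44 and 5.2–5.3% at 35.
- Mancl–DeRouen with t(K−4): 183/4,200 = 4.4% at 44 and 172/4,200 = 4.1% at 36, so slightly conservative.

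**The case against.** The strongest objection is that the article never says the variance is uncorrected and never names a z-test. Mancl–DeRouen, Kauermann–Carroll and Fay–Graubard are themselves robust sandwich variances, so adopting one would contradict nothing in the text, and a full analysis plan may already do so. This stands as a limit on the claim: the inflation is conditional. It does not dispose of the point, because the article fixes the estimator, working correlation, variance type and covariates, and an unqualified robust GEE variance ordinarily means the plain sandwich.

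Three stronger readings are tempting and are not supported.

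- **A flat 10% shortfall in the SE.** Most runs at 44 practices give about 5–8%, with 9% at the upper edge. Values near 10% appear only with fewer practices (0.90 in one set at 36; 0.895 at 30).
- **A planned loss of a fifth of the practices.** The article allows "up to 20% attrition of both GPs and patients", not of practices. With at least two GPs in each, losing a GP need not remove a practice. The 35-practice rows are a sensitivity case, and combining them with 10.4 completers applies the 20% twice.
- **A bias towards declaring superiority.** The test is two-sided and the excess under the null is roughly symmetric. At 7.7%, each direction rises from 2.5% to about 7.7 / 2 = 3.9%.

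The simulations also analyse completers, or full practices of 13, whereas the article plans multiple imputation. The number of practices, which drives the problem, is unaffected by that.

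**Conclusion.** The point holds in conditional form. If the stated GEEs are run with the usual sandwich variance and a normal reference, the treatment-effect standard error is about 5–9% too small. The two-sided type I error is then about 7–8% instead of 5%, for both primary outcomes and the other GEE analyses. It is about 6–7% with equal practice sizes and about 8% with roughly 35 practices. No simulated scenario with the plain sandwich held 5%, and the result changed little for ICC between 0.01 and 0.10. The figures rest on a baseline–outcome correlation of about 0.5, which was not varied, and on the assumed strata proportions and size distribution. The inflation is moderate and cheap to remove.

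**What to change.** State, for both the continuous and the logit GEEs and before unblinding, which small-sample-corrected sandwich variance and which reference distribution will be used. Choose them as a pair:

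- Mancl–DeRouen with a normal reference, which simulated at about 5%; or
- a milder correction such as Kauermann–Carroll, with t degrees of freedom based on the number of practices. This exact pair is not among the results above; the nearest, K/(K−5) scaling with t(K−5), gave 5.2–5.6%. A short simulation at the final number and sizes of practices would confirm it.

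Mancl–DeRouen with t(K−4) is also defensible, but it should be chosen knowing that it runs at about 4%. If the full analysis plan already specifies a correction, it is enough to say so.

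The cost is one sentence and a software option, with no change to design or data. Removing the bias alone widens intervals by roughly 5–10% (1/0.953 = 1.05 with equal sizes; 1/0.915 = 1.09 at 35 practices). Mancl–DeRouen goes somewhat further: at mean size 10.4 and CV 0.5, 1.048/0.937 = 1.12 at 44 practices and 1.056/0.915 = 1.15 at 35, where the numerators are its own ratios of mean SE to true SD. Power falls slightly.

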**Fig. 1 Fig1:**
[figure not shown]
Flow diagram of the study. The recruitment of patients will occur after the practices and GPs have been recruited and randomised, and after GPs have completed their baseline assessment. Patients will only be considered to be enrolled in the trial after they have submitted both their informed consent forms and completed the baseline assessment

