#### Recruitment

General practices and GPs will be recruited through the Victorian Primary Care Practice-Based Research Network (VicReN, based at the University of Melbourne, Victoria, Australia) and the New South Wales (NSW) Primary Health Care Research Network (PHReNet, based at University of NSW Sydney, Australia). At least one phone call and practice visit will be undertaken to provide a detailed description of the study, screen the practices and GPs for inclusion, gain informed consent, and to familiarise GPs regarding the required training in study methods, the professional development obligations if allocated to the intervention group (see GP intervention below), and the support provided by the study team.

Patients will be recruited from the practice’s patient database. Practice staff will identify patients ≥45 years who are patients of the enrolled GPs. The list will be randomised for the mail out, and before the practice is advised of its group allocation GPs will have the opportunity to exclude any patients they know do not meet the inclusion criteria. The practice will send out letters inviting participation on behalf of the researchers, using the practice’s usual method of communication with their patients: post or email. Invitation letters will be sent out in batches until the required number of patients from that practice are recruited. The exclusion list will be checked by the PARTNER Study GP coordinators prior to the letters being sent to ensure all eligible participants in each batch are contacted. Interested patients will complete an online screening questionnaire. Those who pass online screening will be contacted by trial staff for further phone-based confirmation of eligibility and to discuss details of study participation. Eligible patients will be mailed a participant information statement and consent form for participation in the study, and separate consent form authorising the study to access their complete Medicare Benefits Schedule (MBS) and Pharmaceutical Benefits Scheme (PBS) data for the economic evaluation.

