All recruited general practices, GPs and patients will provide written informed consent. This study involves limited disclosure for patients so as to limit pre-conceived ideas as to the superiority of one service delivery method. The information and consent documents provide information about the purposes, potential risks and processes of the study, but do not include specific details of the intervention. Consented patients will receive an email link to, or mailed hard copy of, the baseline survey for completion. Once the baseline survey has been completed and checked by the research team the participant is deemed to have entered the study. The 12-month patient intervention commences at this time (Fig. 1).

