#### Randomisation and allocation concealment

General practices will be randomised, rather than individual GPs or patients, as the intervention involves changes at the practice level. Once GP recruitment at the site is completed, general practices will be randomly allocated to either the intervention or usual care control group at a 1:1 ratio, and by random permuted blocks of sizes 8, 10 and 12. Stratification will be by practice size (< 4 GPs, ≥4 GPs) and location (metropolitan, regional/rural), based on the Australian Statistical Geography Standard (ASGS) Remoteness Structure (2011) [37]. Metropolitan areas will correspond to the ASGS major cities classification (RA1), while regional/rural will be a combination of the inner regional (RA2), outer regional (RA3), remote (RA4) and very remote classifications (RA5). Offsite computer-generated randomisation will be conducted by the study statistician. Opaque, sealed envelopes will be used to conceal allocation and are kept in a locked location.

Patient participants are considered ‘assessors’ in this study as all primary outcomes are self-reported. Thus, as participants are blinded to group allocation the trial is also ‘assessor’ blinded. Statistical analyses will be undertaken by blinded statisticians. Staff of VicReN and PHReNet assigned to assist each practice will be blinded until the point of practice allocation. Research staff involved in patient screening will be blinded until after they have made the eligibility decision. It is not possible to blind the GPs to group allocation, however, they are requested not to discuss the study allocations with their patients.

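### The primary model is valid, but it leaves out patient-level baseline predictors that the trial already collects; pre-specifying a short set would bring a modest gain

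*Protocol article*

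**What the plan says.** For continuous outcomes, the Statistical analysis section of the Protocol article compares mean change between arms by GEE, with exchangeable within-practice correlation and robust standard errors, "adjusting for the baseline value of the outcome variable and stratification variables". Under Randomisation and allocation concealment, the stratification variables are practice size (split at four GPs) and location. Both are practice-level, so the only patient-level covariate in each primary model is that outcome's own baseline. The analysis section also says: "Descriptive statistics at the participant and GP practice level will be presented to allow comparison of treatment groups at baseline".

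On timing, the legend to Fig. 1 states: "The recruitment of patients will occur after the practices and GPs have been recruited and randomised". It adds: "Patients will only be considered to be enrolled in the trial after they have submitted both their informed consent forms and completed the baseline assessment". The Recruitment section agrees: "Once the baseline survey has been completed and checked by the research team the participant is deemed to have entered the study".

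On available data, the Outcome measures section has all primary and secondary outcomes measured at baseline. These include NRS pain, KOOS function in daily living, weight and BMI, and PHQ-9. Age is an eligibility criterion. Sex is not listed anywhere in the article.

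The article also sets safeguards on recruitment:
- The invitation list is put in random order.
- GP exclusions of patients known to be ineligible come early: "before the practice is advised of its group allocation GPs will have the opportunity to exclude any patients they know do not meet the inclusion" (the quote stops one word short). Study coordinators then check the exclusion list.
- Patients are not told the details of the intervention.
- "Research staff involved in patient screening will be blinded until after they have made the eligibility decision".

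**The concern.** In a cluster trial that enrols patients after allocation, randomisation balances practices in expectation but does not by itself guarantee that the enrolled patients are comparable. The safeguards cover selection up to the eligibility decision. After that point patients still have to return consent and complete the baseline survey, and both are conditions of enrolment. GPs cannot be blinded and are only asked not to discuss allocation with patients. Some room for differential enrolment therefore remains.

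If enrolment did differ between arms on a prognostic factor that own-baseline adjustment does not capture, the primary estimate would move with it. Prognostic covariates also reduce residual variance when no imbalance exists, so leaving them out gives up some precision. The relevant values should be nearly complete, because nobody enters without a completed and checked baseline survey. Which covariates to use is best settled now, since a choice made after seeing baseline by arm would be open to question.

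**Working it through.** **Inputs from the article** (Sample size estimation): effect size 0.30, 13 patients per practice, coefficient of variation 0.5, ICC 0.05, attrition up to 20%, 44 practices and 572 patients, 80% power, two-sided 5%.

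**The plan's own figure.** Without clustering, 175 per arm (350 in total) are needed. After 20% patient loss the mean cluster size is 13 × 0.8 = 10.4, and the design effect is 1 + ((1 + 0.5²) × 10.4 − 1) × 0.05 = 1.60. That gives 350 × 1.60 = 560 analysed and 560/0.8 = 700 enrolled. The stated 572 does not follow from the stated inputs alone. It does follow if a baseline to follow-up correlation of about 0.43, which the article does not state, is credited. That is a separate matter. Here it means only that the starting power is uncertain, so two cases are shown.

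**Precision.** The article gives no R-squared for extra covariates. I assume that they explain a further 0.01 to 0.10 of the residual variance. The standard error is multiplied by √(1 − R²):
- R² = 0.01: √0.99 = 0.995, a cut of 0.5%.
- R² = 0.10: √0.90 = 0.949, a cut of 5.1%.

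**Power.** With 572 × 0.8 = 457.6 analysed and design effect 1.60, the effective number per arm is 457.6/(2 × 1.60) = 143. Power = Φ(0.30 × √(143/2)/√v − 1.96), where v = (1 − r²)(1 − R²) and r is the correlation of the outcome with its own baseline.
- r = 0 (no credit for own baseline): 71.8%, rising to 72.2% (R² = 0.01) or 76.2% (R² = 0.10).
- r = 0.5 (assumed): 83.4%, rising to 83.7% or 87.0%.

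The gain is about 0.4 to 4.4 percentage points.

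**Shift from an imbalance in the other primary outcome's baseline.** Let r1 be the correlation of the outcome with its own baseline, r2 with the other baseline, and ρ the correlation between the two baselines; all are assumed. The partial coefficient of the other baseline is b = (r2 − r1ρ)/(1 − ρ²). If its imbalance is 0.2 SD, the expected imbalance in the own baseline is 0.2ρ, and adjusting for own baseline leaves 0.2(1 − ρ²). The shift is then 0.2(r2 − r1ρ). I take the 0.30 target to be in SD units of the outcome.

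| r1, r2, ρ | b | Residual variance ratio | Shift (SD) | % of 0.30 |
|---|---|---|---|---|
| 0.40, 0.30, 0.50 | 0.13 | 0.984 | 0.020 | 7 |
| 0.40, 0.38, 0.55 | 0.23 | 0.956 | 0.032 | 11 |
| 0.50, 0.40, 0.50 | 0.20 | 0.960 | 0.030 | 10 |
| 0.50, 0.45, 0.60 | 0.23 | 0.953 | 0.030 | 10 |

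The benefit can vanish. With r1 = 0.5, r2 = 0.3 and ρ = 0.6, r2 − r1ρ = 0, so this covariate gives no gain and its omission causes no shift.

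**How large a chance imbalance could be.** For all 572 patients at 13 per practice, the design effect is 1 + (1.25 × 13 − 1) × 0.05 = 1.7625. The standard error of a standardised baseline difference is √(4 × 1.7625/572) = 0.111, taking the article's ICC for the covariate too. An imbalance of 0.2 SD is therefore 0.2/0.111 = 1.8 standard errors: within the 95% range by chance, but near its edge.

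**The case against.** The strongest reply is that nothing here is an error. Adjusting for own baseline and the stratification factors is standard and valid, and own baseline is usually the strongest predictor. Further covariates are often left to the SAP, which is not shown, so the short covariate set can be confirmed only for the article. The size of any gain comes from assumed correlations, and the choice of covariates is partly a matter of judgement. All of this stands. It limits the point to an improvement.

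A reader might infer more, in four ways that the article does not support:
- That the plan only describes baseline imbalance. It does not: own-baseline adjustment corrects imbalance in the most relevant variable, and through correlation part of the imbalance in others.
- That late enrolment makes the estimate biased. The safeguards address much of that route. Bias would need differential enrolment on factors that own baseline does not capture, and nothing in the article shows this.
- That chance imbalance is bias. It is not: it averages to zero over randomisations, and its variability is carried by the robust standard error.
- That a 0.2 SD imbalance would cost 13 to 20% of the target effect. That figure needs a partial coefficient of 0.2 to 0.3 (0.2 × 0.2 = 0.04 and 0.3 × 0.2 = 0.06, each over 0.30) and no help from own-baseline adjustment. The scenarios above give coefficients of 0.13 to 0.23 and about half that shift.

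None of these replies removes the suggestion itself. The data are already collected, GPs know the allocation, and enrolment is completed after the blinded step.

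**Conclusion.** The point holds as a low-priority improvement to a valid analysis. What survives is a small gain in precision and partial protection against a residual risk of differential enrolment. The protection is partial because covariates correct only for what is measured. The sizes are those in the working. They depend on the assumed added R-squared, the assumed correlations and an illustrative 0.2 SD imbalance, none of which the article supplies. The article does not support a claim that the primary result will be biased or that the model is wrong.

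**What to change.** In the Statistical analysis section, or in the SAP if it is still open, state before unblinding that the GEE for each primary outcome adjusts for:
- baseline NRS pain and baseline KOOS function in daily living, both in both models;
- baseline BMI, baseline PHQ-9 and age, and sex if it is recorded;
- practice size and location, as now.

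Keep the currently stated model as a sensitivity analysis, so that readers can see whether the added covariates matter.

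The cost is a change of wording, a few more patient-level terms in a model with about 458 to 572 patients, and slightly more analysis work. It needs no new patients and no new data, provided sex is included only if it is already recorded.
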